### Outcomes

#### Primary outcomes

##### Itch

The change in itch severity will be assessed as primary outcome throughout the intervention and follow-up phase. Participants will be asked to rate the most severe itch as well as the average itch experienced over the last 24 hours on a Visual Analogue Scale (VAS). The scale ranges from 0 (‘no itch’) to 100 (‘most severe itch imaginable’). Specifically, participants will be asked: ‘How severe was the most intense itch you experienced in the last 24 hours?’ (German: ‘Wie stark war der schlimmste Juckreiz, den Sie in den letzten 24h gespürt haben?’) and ‘How severe was your average itch in the last 24 hours?’ (German: ‘Wie stark war Ihr durchschnittlicher Juckreiz in den letzten 24h?’). This measurement will be carried out during visits 1–9.

##### Skin-related quality of life

Skin-related quality of life will be measured by the Dermatology Life Quality Index (DLQI),^47^ a validated self-report measure that quantifies subjective quality of life in adults with skin conditions such as psoriasis vulgaris. Patients will be asked to rate symptom severity and impairment across various areas of life over the past 7 days on a scale from 0 (‘not at all’) to 3 (‘very much’). This measurement will be conducted at all visits. As with itch, quality of life was selected as a primary outcome to serve as a meaningful subjective indicator for symptom alleviation.

### Secondary outcomes

#### Objective symptom severity

The PASI^48^ will be used as a clinical scoring tool to assess the extent of affected body surface area and the severity of key symptoms in patients with psoriasis. As the most commonly used clinical tool for objectively evaluating psoriasis severity,^48^ the PASI provides a composite score ranging from 0 to 72, with scores of at least 10 representing a moderate-to-severe degree of psoriasis severity. The PASI will be conducted at all visits.

#### Psychological secondary outcomes

Online supplemental file 1 provides an overview of the time points and the respective questionnaires used. These outcomes are also collected as part of the CRC’s central projects, which coordinate and administrate standardised collection of additional measures across all study sites and subprojects involving human participants for merged analyses. According to the CRC’s approach, these measures will serve as additional analyses aiming to identify predictors of expectation effects.

##### Average Stress (VAS)

Patients will rate their average stress using the item ‘How stressed have you felt on average in the last 24 hours?’ (German: ‘Wie gestresst haben Sie sich in den letzten 24h im Durchschnitt gefühlt?’) on a VAS from 0 (‘no stress at all’) to 100 (‘greatest imaginable stress’).

##### Expected skin-related quality of life after the study (DLQI-Expectations)

To assess the expected skin-related quality of life after the study, patients will be asked to rate modified items from the DLQI^47^ on a 5-point-Likert scale from 0 (‘not at all’) to 4 (‘very much’). The content of the items mirrors the items of the original questionnaire, with the exception of asking for subjective anticipations of the skin-related quality of life after study participation (‘How much do you think your skin disease will affect your life at the end of our study?’; German: ‘Was denken Sie, wie sehr Ihre Hauterkrankung Ihr Leben am Ende unserer Studie beeinflussen wird?’). An overall score of expected skin-related quality of life will be calculated as the sum of all individual values across all items. Expected skin-related quality of life will be assessed at four time points (visits 1, 5, 7 and 9).

##### Itch (ecological momentary assessment)

To complement visit-based assessments of itch, real-time itch intensity will be measured using ecological momentary assessment (EMA). Current itch will be assessed by asking patients: ‘How severe is your itch at the moment?’ (German: ‘Wie stark ist Ihr Juckreiz in diesem Moment?’). Patients will respond on a VAS ranging from 0 (‘no itch’) to 100 (‘most severe itch imaginable’). Assessments will be delivered via the smartphone application m-Path,^49^ which will be preprogrammed with fixed-time prompts. Participants will receive notifications at 08:00, 14:00 and 20:00 on the respective days before and after each study visit, as well as on the day of the visit itself. A non-randomised time sampling approach was selected to reduce participant burden and enhance compliance across the extended study period. Given the high prevalence of itch in psoriasis patients and its significant impact on quality of life, itch was chosen to reflect a meaningful subjective indicator of symptom alleviation. Its susceptibility to psychological influences also characterises changes in itch as a useful marker for assessing the impact of psychological expectation effects on symptom severity in the context of pharmacological conditioning.

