### Patient adherence and study discontinuation

To improve adherence to the intervention protocol, all medication or placebo injections will be administered by the research assistant at the clinical study centre, which requires the attendance of patients. Similarly, all questionnaire data will be assessed prior to the medication administration on site.

Given the relatively low dosages of secukinumab in the reinforcement groups, topical treatments will be permitted as concomitant care in all three groups to enhance adherence and reflect real-life clinical care, as recommended by the S3 guideline for the treatment of psoriasis vulgaris. The study participation will be discontinued at any time at the patient’s request, if side effects are deemed intolerable by the patient and/or the treating physician or if the patient misses more than one visit. In such cases, the patient will be unblinded to the treatment allocation to allow appropriate subsequent medical care.

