### Exploratory analyses

In addition to the confirmatory analyses, exploratory analyses will be conducted to examine potential associations between the primary outcomes and various secondary and moderating variables, including demographic characteristics (eg, age, gender), psychometric measures (eg, depression, anxiety), biological markers (ie, blood, saliva) and ecological momentary assessments (ie, itch ratings, treatment satisfaction). These analyses are exploratory in nature and are intended to generate hypotheses for future research.

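### The Hypothesis 1 itch model uses no baseline covariate, although visit 1 itch and momentary itch from before the first injection are collected and could narrow its interval cheaply

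*Protocol article*

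**What the plan says.** All places are in the Protocol article.

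- **Itch (primary outcome).** Patients "rate the most severe itch as well as the average itch experienced over the last 24 hours" on a 0 to 100 VAS. "This measurement will be carried out during visits 1–9". There is no itch VAS at visit 0.
- **Skin-related quality of life.** For the DLQI, "This measurement will be conducted at all visits", and the PASI section says the same. Both therefore have two occasions before treatment.
- **Patient adherence and study discontinuation.** "all questionnaire data will be assessed prior to the medication administration on site". Visit 1 itch is therefore a pre-dose value, and the only one on the primary scale.
- **Itch (ecological momentary assessment).** The item is "How severe is your itch at the moment", also on a 0 to 100 VAS, with prompts at 08:00, 14:00 and 20:00 "on the respective days before and after each study visit, as well as on the day of the visit itself".
- **Analysis plan.** Hypothesis 1 tests non-inferiority of the pooled reinforcement groups to TAU on pre-to-post reductions, within a linear mixed model. Visits are levels of a Time factor, participants have random intercepts, and no baseline covariate is listed.
- **Exploratory analyses.** Associations of the primary outcomes with other variables are planned, including "ecological momentary assessments (ie, itch ratings, treatment satisfaction". No other use of momentary itch is stated.

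**The concern.** Itch is the Hypothesis 1 outcome with the thinnest pre-treatment measurement. Its pre value is one occasion recalling 24 hours. In a model where visits are levels of Time, day-to-day noise on that occasion passes in full into the pre-post contrast and widens the non-inferiority interval.

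Two things that could reduce this are already collected. One is visit 1 itch itself, used as a covariate instead of as an outcome row. The other is momentary itch recorded before the first injection. Neither can be affected by treatment, so adjusting for them introduces no treatment-related bias. What is at stake is the precision of a primary contrast, available for almost nothing.

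**Working it through.** **1. How many momentary ratings precede the first injection?** Dosing is the last step of a treatment visit (section Visit 1). Around visit 1: 3 prompts the day before + 1 at 08:00 on the day = 4 (5 if dosing falls after 14:00). If prompts also run from visit 0 once consent is given, add 14:00 and 20:00 that day and 3 the next day: 4 + 2 + 3 = 9. If the two visits are two days apart, the middle day is shared: 2 + 3 + 1 = 6. The visit clock times, the date the app is started and the gap between visits 0 and 1 are not stated. About four is a fair reading; any larger number is inference.

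**2. Is there a plan figure to reproduce?** No. The sample size section works with proportions of favourable outcomes (70% v 75%, margin 0.25) and gives no itch SD or correlation. Everything below is relative and rests on assumed correlations.

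**3. Set-up.** Let X be visit 1 itch, M the mean of pre-injection momentary itch and Y itch at one post visit, each scaled to unit variance. Assumptions: corr(X,Y) = corr(M,Y) = ρ, from 0.2 to 0.7; corr(X,M) = c, from 0.6 to 0.9, with c ≥ ρ. With complete data and Time as a factor, the planned Group × Time contrast between visit 1 and one post visit is a difference in mean changes.

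- Model as written: Var(Y − X) = 2(1 − ρ).
- (A) As written, plus M × Time: width ratio √[1 − (c − ρ)²/(2(1 − ρ))].
- (B) Post-dose itch adjusted for X only: √[(1 − ρ²)/(2(1 − ρ))].
- (C) Post-dose itch adjusted for X and M: √[(1 − 2ρ²/(1 + c))/(2(1 − ρ))].
- Increment of M beyond X: C/B.

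Worked example, ρ = 0.5 and c = 0.8. The denominator is 2(1 − 0.5) = 1.
- A = √(1 − 0.09) = 0.954
- B = √0.75 = 0.866
- C = √(1 − 0.5/1.8) = √0.722 = 0.850
- C/B = 0.981

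**4. Percentage narrowing of the interval against the model as written (last column: against B).**

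| ρ | c | A | B | C | M beyond X |
|---|---|---|---|---|---|
| 0.2 | 0.6 | 5.1 | 22.5 | 22.9 | 0.5 |
| 0.2 | 0.9 | 16.7 | 22.5 | 22.6 | 0.1 |
| 0.3 | 0.6 | 3.3 | 19.4 | 20.4 | 1.2 |
| 0.3 | 0.9 | 13.8 | 19.4 | 19.6 | 0.3 |
| 0.5 | 0.6 | 0.5 | 13.4 | 17.1 | 4.3 |
| 0.5 | 0.9 | 8.3 | 13.4 | 14.2 | 0.9 |
| 0.7 | 0.7 | 0.0 | 7.8 | 16.0 | 8.9 |
| 0.7 | 0.9 | 3.4 | 7.8 | 10.2 | 2.6 |

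**5. Reading.** Adding momentary itch alone to the model as written gives 0 to 17%. Adjusting for both gives 10 to 23%. The share owed to momentary itch is 0.1 to 4.3% for ρ up to 0.5 and 2.6 to 8.9% at ρ = 0.7. If M carries nothing about Y beyond X, so that corr(M,Y) = ρc, its increment over B is zero.

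**The case against.** The strongest reply is that this is an efficiency preference. One pre-dose visit as baseline is ordinary, a noisy baseline makes non-inferiority harder rather than easier to conclude, and a journal article may leave supportive analyses to a fuller plan. It stands that nothing is contradicted and that no false claim of non-inferiority is at risk. It does not dispose of the point: the article does set out the Hypothesis 1 model, and that model has no baseline covariate.

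Second, the momentary item asks about itch now, while the primary items ask about the worst and average over 24 hours. That stands against averaging the two, which would change the endpoint. It does not count against using momentary itch as a covariate.

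Third, the change goes beyond adding a term, because visit 1 itch must move from outcome to covariate. That is correct, and the fix says so.

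Three stronger readings are tempting and are not supported:

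- A reader might treat momentary itch as a second, exchangeable baseline, average it in, and claim a quarter less variance or the equivalent of tens of extra patients. That requires ratings taken days apart before treatment to correlate no better than ratings taken months apart across treatment. Nothing in the article supports this, and averaging is not the remedy proposed.
- A reader might count nine scheduled pre-dose prompts, or say that visit 1 yields a single rating. The count is inferred, and visit 1 has two items.
- A reader might conclude that momentary itch is barred from any comparison between arms. The article lists it as a secondary outcome and names an exploratory use. It does not say that this is the only one.

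**Conclusion.** The point holds as an inexpensive gain in precision, not as an error. Primary itch has one pre-dose occasion, the stated model adjusts for no baseline, and further pre-injection itch data are collected but named only for exploratory association.

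Under the assumed correlations, adjusting for both baselines narrows the itch interval by about 10 to 23%. Most of this usually comes from visit 1 itch. Momentary itch adds about 0 to 5% beyond it in most settings and approaches 9% only when the pre-post correlation is high. These figures assume equal variances, complete data, one post visit, and momentary itch that predicts later itch as well as visit 1 itch does. The last is favourable; the added gain from momentary itch could be zero. Since the article gives no correlations, no single figure should be quoted.

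**What to change.** In the Hypothesis 1 itch model:

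1. Take itch at the post-dose visits (2 to 9) as the outcome.
2. Enter visit 1 itch and the mean of all momentary itch ratings time-stamped before the first injection as baseline covariates, each with its interaction with Time.
3. State a simple rule for patients without pre-injection momentary ratings, such as mean imputation of that covariate.
4. Optionally, report the TAU v pooled reinforcement contrast on per-visit mean momentary itch as a supportive analysis.

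The cost is revised analysis wording, some restructuring of the itch model, and handling of missing momentary ratings. No new data are needed. If only part is adopted, the visit 1 covariate usually brings most of the gain.

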##### Patient Benefit Index

Subjective treatment needs and their achievement will be assessed using the 25-item Patient Benefit Index (PBI).^50^ Participants will rate the subjective value of need prior to treatment at baseline measurement point and the extent to which each treatment need was met during the treatment on a 6-point Likert scale from 0 (‘not at all’) to 5 (‘very much’). Needs prior to treatment and needs achieved during treatment will be converted to a weighted index score. The PBI will be assessed at five time points (visits 0, 3, 5, 7 and 9).

##### Patient global assessment

The patient global assessment (PGA)^51^ will be used to assess the current perceived severity of psoriasis symptoms on a 5-point Likert scale from 0 (‘no psoriasis/normal skin’) to 4 (‘severe psoriasis’). The PGA will be measured at nine time points (visits 1–9). Additionally, a modified version of the PGA will be used. As with the modified DLQI, the item mirrors the item of the original questionnaire with the exception of assessing subjective expectations of symptom severity after study participation (‘What severity of psoriasis do you expect at the end of our study?’; German: ‘Welche Schwere Ihrer Psoriasis (Schuppenflechte) erwarten Sie am Ende unserer Studie?’). The modified PGA will be assessed at four time points (visits 1, 5, 7 and 9).

##### Patient’s perception of the conditioned stimulus

To assess how feasible, effective and valuable the patients perceived the novel beverage in enhancing the drug’s effect, they will rate three items on a VAS ranging from 0 (‘not at all’) to 100 (‘completely’). Specifically, patients will be asked ‘How pleasant is it for you to drink the beverage?’ (German: ‘Wie angenehm ist es für Sie, das Getränk zu trinken?’), ‘How effective do you find the drink in increasing the effectiveness of your medication?’ (German: ‘Wie effektiv finden Sie das Getränk, um die Wirksamkeit Ihres Medikaments zu steigern?’) and ‘How useful do you find the drink to help your body fight psoriasis?’ (German: ‘Wie nützlich finden Sie das Getränk, um Ihren Körper dabei zu unterstützen, gegen die Schuppenflechte zu kämpfen’). The patient’s perception of the conditioned stimulus will be assessed at three time points (visits 5, 7 and 9).

##### State-Trait Anxiety Inventory

The short version of the State-Trait Anxiety Inventory (STAI)^52^ will be used to measure state anxiety. Patients will rate their current anxiety on a scale from 0 (‘not at all’) to 4 (‘very much’). A total score for state anxiety will be calculated as the sum of individual values across all items. The STAI will be assessed at nine time points (visits 1–9).

##### Attribute Influences on Perceived Treatment Effects (VAS)

To assess the degree to which patients attribute perceived treatment effects to potential influencing factors, they will be asked to respond to the item: ‘To what extent do you think the following factors will have an influence on your treatment?’; German: ‘Was denken Sie, in welchem Maße die folgenden Faktoren einen Einfluss auf Ihre Behandlung haben werden?’). Patients will rate this item for four potential treatment influences: the physician, themselves, the medication and the conditioned stimulus (with the conditioned stimulus only included for patients assigned to a reinforcement group), using a VAS ranging from 0 (‘no influence’) to 100 (‘greatest possible influence’). Treatment influences will be assessed at two time points (visits 2 and 9).

##### Treatment Satisfaction (Ecological Momentary Assessment, EMA)

To capture real-time data on treatment satisfaction, patients will answer an EMA item at 8:00 PM on the day of each visit (‘How satisfied are you with your therapy at the moment?‘; German: ‘Wie zufrieden sind Sie im Moment mit Ihrer Therapie?‘). Patients will rate the item on a VAS ranging from 0 (‘no satisfaction’) to 100 (‘total satisfaction’).

### Biological secondary outcomes

#### Blood samples

During visits 0, 5 and 8, blood samples will be collected to monitor physiological responses to the medication, enable cytokine analysis and ensure the safety of systemic therapy.

#### Saliva samples

During visit 0, saliva samples will be collected using the Oragene-DNA OG-600 kit (DNA Genotek, Ottawa, Canada). Additionally, patients will be instructed to collect saliva samples for analysis of awakening cortisol and alpha-amylase on two consecutive days after visit 0. The samples will be collected right after waking up, as well as 30 and 45 min after awakening. Patients will be informed that saliva collection should take place prior to food or coffee consumption. To facilitate the saliva collection, the research assistant will set up an app on the patients’ smartphones. The app will provide acoustic reminders to ensure timely collection of the saliva samples. Additionally, the app will guide patients to track the sample collection by scanning barcodes on the salivettes. Patients will be instructed to return the salivettes at their next study visit. Samples will be used to assess the cortisol awakening response as part of the CRC’s central projects.

#### Skin biopsies

As an optional measure, patients can provide consent for the collection of skin biopsies. The collected skin samples will be used to assess changes in biomarkers of psoriasis before and after 12 weeks of therapy. At visit 1 and visit 7, two 4 mm punch biopsies will be taken from the consenting patients: one from psoriasis-affected skin and one from unaffected skin, resulting in a total of four biopsies per participant. A total of 10 patients per group are planned to provide skin biopsies.

### Moderators

As part of the CRC’s comprehensive, standardised questionnaire battery, the following moderator variables will be assessed:

#### Beck Depression Inventory

Patients will rate their severity of depression using the Beck Depression Inventory (BDI-II)^53^ on a 4-point-Likert scale from 0 (‘no symptoms’) to 3 (‘severe symptoms’). An overall score for depression will be computed as the sum of individual values across all items. The BDI-II will be measured at three time points (visits 1, 5 and 9).

#### Big-Five Inventory

To assess the Big-5 personality traits, patients will rate the items of the Big-Five Inventory (BFI-10)^54^ on a 5-point Likert scale from 1 (‘does not apply at all’) to 5 (‘fully applicable’). Mean scores for each personality subscale will be calculated. The BFI-10 will be measured once at visit 0.

#### Desire for Itch Relief (VAS)

Patients will rate their desire for itch relief using the item ‘How much would you like your itching to improve as a result of the treatment?’ (German: ‘Wie sehr wünschen Sie sich, dass sich Ihr Juckreiz durch die Behandlung bessert?’) on a VAS from 0 (‘not at all’) to 100 (‘greatest possible desire’). Desire for itch relief will be assessed once at visit 1.

#### Generic Assessment of Side Effects

The Generic Assessment of Side Effects (GASE)^55^ will be used to assess the frequency and severity of various side effects and their attribution to the study medication. Participants will rate the severity of side effects on a scale from 0 (‘not present’) to 3 (‘severe’) and will indicate whether they attributed the side effects to the study medication using a dichotomous item (‘yes’/‘no’). General symptom load will be calculated as the sum of all symptom ratings, while a medication-attributed total score will be calculated as the product of the individual item answers and the binary attribution rating (1 = ‘yes’; 0 = ‘no’). The GASE will be measured at nine time points (visits 1–9).

#### Generic Rating Scale for Previous Treatment Experiences, Treatment Expectations and Treatment Effects

Patients will rate their previous treatment experiences at baseline as well as treatment expectations and acute treatment effects during the treatment phase using the GEEE (Generic Rating Scale for Previous Treatment Experiences, Treatment Expectations and Treatment Effects)^56^ on a 10-point-Likert scale from 0 (‘none’) to 10 (‘greatest imaginable’). Previous treatment experiences and treatment expectations will each be measured once, at visit 0 and visit 1, respectively. Treatment effects will be assessed at eight time points (visits 2–9).

#### Interoceptive Awareness and Sensitivity Questionnaire

Patients will rate items from the Interoceptive Awareness and Sensitivity Questionnaire (ISAQ)^57^ on a 5-point Likert scale from 1 (‘strongly disagree’) to 5 (‘strongly agree’). An overall score for all three subscales (ie, sensitivity to neutral bodily sensations, attention to unpleasant bodily sensations, difficulty disengaging from unpleasant bodily sensations) will be computed as sum of all individual values across the items of each subscale. The ISAQ will be assessed once at visit 0.

#### Menstrual cycle assessment

A short questionnaire will be used to assess menstrual cycle characteristics. All patients will be asked whether they currently menstruate and whether they consider themselves premenopausal, perimenopausal or postmenopausal. If participants report currently menstruating and being premenopausal, they will be additionally asked to provide information on the first day of their most recent menstrual period, the average length of their menstrual period (in days) and whether they are currently using any hormonal contraceptive, with a prompt to specify the type used. Menstrual cycle characteristics will be assessed once at visit 1.

